### Training of the study assessors

The PT assessors have five to 20 years of experience in paediatric neurology and are familiar with the GMFM-66 from clinical practice. Regardless, a group training session will be done with the GMFM-66 (barefoot and shoes/AFO versions). All assessors independently score three GMFM videotapes (a child in each of GMFCS I, II and III) from the co-PI (VW)’s GMFM video-training bank (including a section on recognizing/resolving GMFM test administration errors common to the GMFM’s Stand and Walk dimensions). All must achieve a criterion score of 80% accuracy (the same level used with the original GMFM criterion test). The 6MWT, ROM, Tardieu Scale and child-/parent-report-questionnaires (DMQ, ASK-30, CAPE, KIDSCREEN, PEDI) have simple administration requirements and do not require further testing beyond the initial group training session. During assessments, the assessor also works with the study RA to administer the 15-min gait assessment (time distance parameters of gait) using our Gait-Rite system and gait video.

## Sample size

The study has been designed and powered to ensure adequate sample size for the primary research questions and analysis of children in GMFCS Levels II and III. The starting point for our sample size calculation consideration was a single group Lokomat study with a similar GMFCS sample and Lokomat use protocol in which the GMFM Stand and Walk mean scores changed by approximately 5 points (SD change = 7) (Borggraefe et al. 2010b). Our study is powered to let us detect a difference between the two interventions of three points (SD = 6: small effect size) on the GMFM-66, a magnitude of change that is considered to be a minimally clinically important difference (Oeffinger et al. 2008) when evaluating benefits of treatment. The reason for a difference change target in our study is that we are comparing two active interventions, each of which could result in positive change given the walking focus and boost for many of the children in therapy intensity. This sample size is also sufficient to handle the 6MWT comparisons and the small effect size observed by others in single group Lokomat studies in the 6MWT results (mean gains of 25 m [SD = 50 m], personal communication, Glenrose Hospital program, 2012).

For crossover designs, sample size calculations that link with a matched pairs *t* test calculation are appropriate (Senn 2002). A paired *t* test is also the underlying basis for the more sensitive repeated measures ANOVA that we have chosen to use so that we can include a period effect within the analysis. With an alpha of 0.025, beta of 0.20, and a detectable change score difference between intervention of thre points on the GMFM-66 (with an estimated SD of change of 6.0 points), a sample of 32 children is required (Hintze 2001). We increased the sample requirement to 40 to account for a potential drop out/protocol deviation rate of 20%. Sample calculation based on this generous drop-out rate will support the primary efficacy analysis that focuses only on the children who attend more than 70% of the sessions within one or the other intervention phase.

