## Analyses

Data entry forms were built for each measure in the study to correspond to the paper forms that the assessors used. REDCap (Harris 2012) requires outer limits for each value, and each paper data sheet is double entered for purposes of data verification process. Collectively these features optimize the data entry accuracy. Study data will be kept for seven years following conclusion of the trial, at which point data will be destroyed following REB requirements.

Descriptive statistics and graphic displays will be presented for all outcomes for the PT and Lokomat interventions (pre, post-test and change scores). Equivalence between baseline_A_ and baseline_B_ scores will be evaluated for each outcome; a t-test or Wilcoxon test will be used in this comparison as appropriate. The primary analysis will be for the pre- to post-test differences (change scores) of the GMFM-66 and 6MWT between groups. Assuming normality of data, a repeated measures ANCOVA will be performed on GMFM-66 and 6MWT change scores to compare the effects of the Lokomat and gait-related PT interventions. The child’s relevant baseline score (baseline_A_/baseline_B_) will be used in the ANCOVA to increase analytic precision. The P value will be adjusted to 0.025 to handle the expected high correlation between the GMFM-66 and timed walk. Evaluation of an intervention order effect (i.e., being the first or second treatment), as well as the interactions with intervention group will be built into this analysis (Senn 2002). Secondary sub-analyses will be done in the same way within GMFCS II and III subgroups to determine any differential response for GMFCS Level.

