A similar set of analytic approaches will be used for the secondary outcome measures (GMFM Stand and Walk, Timed Up and Go, walk velocity/step and stride length [from GAITRite], observational gait scale, average daily step counts [step activity monitor data], Quality FM, *Challenge* Assessment, ASK-30, PEDI Part II, KIDSCREEN, COPM and GAS scores), using the baseline value of the measure of interest as a covariate within a MANCOVA procedure that will permit simultaneously handling of multiple secondary outcome measure change score evaluations. If both parent and child filled out the questionnaires (i.e., all children 8 years of age and up who were able to do so), the children’s data will be analysed as primary. Otherwise parent questionnaire data will be considered as primary. A comparison of child and parent questionnaire results will be done as a secondary analysis via an ANOVA in which both single point in time (baseline) and change scores will be evaluated. ROM and Tardieu scores will be summarized in a simpler manner, using descriptive statistics and graphical presentations to illustrate scores in each phase. The power of all primary and secondary ‘no difference’ analyses will be determined post hoc.

The primary analysis will include all children who attended ≥70% of sessions for each intervention, and those who discontinued one or both interventions for a reason directly related to the study (e.g., excessive fatigue associated with participation or issues related to dislike of one or both interventions), or dropped out of the trial due to an intervention-associated injury. In the case of dropout due to study fatigue or dislike of the intervention, a strong effort will be made to do a discharge assessment at the time of withdrawal. In the case of injury, it may be possible to follow the child and evaluate some of the outcomes when the child is able (post-minor injury). If the physical assessment is not possible due to compromised physical status, completion of the functional and participation measures may still be appropriate.

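### The claim that the sample suffices for the co-primary 6MWT rests on a single-group Lokomat gain of 25 m used as the Lokomat-minus-PT difference; no between-intervention 6MWT difference is stated

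*Protocol article*

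**What the plan says.** The protocol article names GMFM-66 and 6MWT as co-primary outcomes (Abstract, Methods/design), and its primary hypothesis covers both (Study aims and hypothesis).

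For the GMFM, the Sample size section starts from a single-group Lokomat study in which "GMFM Stand and Walk mean scores changed by approximately 5 points (SD change = 7"). It then powers the trial to "detect a difference between the two interventions of three points (SD = 6: small effect size) on the GMFM-66", describes 3 points as a minimally clinically important difference, and adds: "The reason for a difference change target in our study is that we are comparing two active interventions". It notes that each of these could bring positive change.

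For the 6MWT, the next sentence reads: "This sample size is also sufficient to handle the 6MWT comparisons and the small effect size observed by others in single group Lokomat studies". It cites mean gains of 25 m (SD 50 m) from a personal communication. It gives no difference between interventions and no SD for a within-child difference.

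The calculation is on a matched-pairs t test: "With an alpha of 0.025, beta of 0.20, and a detectable change score difference between intervention of thre points on the GMFM-66" and an SD of 6, giving 32 children, raised to 40 for 20% dropout or protocol deviation. Sidedness is not stated there, nor in the Analyses section, which says: "The P value will be adjusted to 0.025 to handle the expected high correlation between the GMFM-66 and timed walk". That section also plans that the power of all primary and secondary comparisons showing no difference "analyses will be determined post hoc".

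**The concern.** A gain from before to after Lokomat training contains whatever any comparable block of walking therapy would produce. The trial estimates only the part by which Lokomat exceeds PT. The Sample size section recognises this for the GMFM and then passes over it for the 6MWT.

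The PT arm is not an inert comparator. Under Gait-related PT intervention protocol it has 35 minutes of active treatment per session, up to 10 minutes of treadmill work is allowed, and walking endurance is among the listed areas of focus. Some 6MWT gain in that arm is to be expected.

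At stake is a stated design property of one of the two co-primary outcomes. If the 6MWT result is not significant, a reader who trusts the sentence may take it as good evidence of no difference, although the sample was never shown to be adequate for that comparison.

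**Working it through.** **Inputs** (Sample size section): GMFM-66 difference 3, SD 6; single-group GMFM Stand and Walk gain 5, SD 7; single-group 6MWT gain 25 m, SD 50 m; alpha 0.025; power 0.80; 32 evaluable children, 40 enrolled.

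**1. The plan's own figure.** For a paired comparison, n = ((z_alpha + z_power)/d)² with d = 3/6 = 0.50.
- One-sided 0.025: ((1.960 + 0.842)/0.50)² = 31.4, so 32. The exact t calculation gives 34.
- Two-sided 0.025: ((2.241 + 0.842)/0.50)² = 38.0, so 39. The exact t calculation gives 41.
- Dropout: 32/(1 − 0.20) = 40.

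So 32 is approximately reproduced with one-sided 0.025 (numerically the same as two-sided 0.05), and not with two-sided 0.025.

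**2. What the 6MWT sentence assumes.** 25/50 = 0.50 = 3/6. The 6MWT has the same standardised effect as the GMFM-66 only if the whole single-group gain is the difference between interventions, which means a PT gain of zero.

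**3. Power if PT produces some gain.** The documents give no 6MWT difference, so the reduced values are assumptions. Applying the ratio 3/5 to the mean gives 25 × 0.6 = 15 m. Scaling the SD as well, by 6/7, gives 50 × 6/7 = 42.9 m. A milder cut is 20 m. Power comes from the noncentral t with 31 degrees of freedom and noncentrality d√32.

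| Difference, SD | d | d√32 | Two-sided 0.025 | One-sided 0.025 |
|---|---|---|---|---|
| 25 m, 50 m | 0.50 | 2.83 | 0.68 | 0.78 |
| 20 m, 50 m | 0.40 | 2.26 | 0.47 | 0.59 |
| 15 m, 42.9 m | 0.35 | 1.98 | 0.37 | 0.48 |
| 15 m, 50 m | 0.30 | 1.70 | 0.27 | 0.38 |

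With all 40 children evaluable, 15 m at SD 50 m has power 0.34 (two-sided) or 0.46 (one-sided).

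**4. The SD.** The 50 m accompanies a single-group change. If both arms have that SD and their change scores correlate at ρ, the within-child difference has SD 50√(2(1 − ρ)), which equals 50 m only at ρ = 0.5. For 15 m and 32 children:

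| ρ | SD of difference | Two-sided 0.025 | One-sided 0.025 |
|---|---|---|---|
| 0 | 70.7 m | 0.14 | 0.21 |
| 0.25 | 61.2 m | 0.18 | 0.27 |
| 0.5 | 50.0 m | 0.27 | 0.38 |
| 0.75 | 35.4 m | 0.52 | 0.64 |

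**5. Detectable difference.** With 32 children, 80% power needs d = 0.511 (one-sided) or 0.568 (two-sided) by the exact t. At SD 50 m that is 0.511 × 50 = 25.6 m or 0.568 × 50 = 28.4 m. At SD 35.4 m it is 18.1 m or 20.1 m.

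**The case against.** The best defence is that the documents contain no 3/5 discount. The 3 points are justified as a clinically important difference, the 5 points belong to a different score (Stand and Walk, not GMFM-66), and the SD was changed too. The two-sided 0.025 reading is also an assumption, and under it the plan's own 32 fails. The baseline covariate may improve precision, children who stop for study-related reasons stay in the primary analysis, and a high correlation between the two change scores would raise power.

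All of this stands, and it limits what can be said. A reader might infer that the trial has 27% power for the 6MWT, or that a null result is likely even if a real difference exists. The documents support neither, because they give no expected 6MWT difference. The 0.27 combines two-sided testing, the 3/5 ratio, an unchanged SD and a correlation of 0.5. A reader might also infer that the trial is underpowered even for the full 25 m. The 0.68 there reflects sidedness alone: under the convention that approximately reproduces 32, power is 0.78 by the exact t (0.81 by the normal approximation). That question affects the GMFM-66 equally and is a separate matter.

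None of this supplies the missing quantity. The sufficiency claim still has only a single-group gain behind it.

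**Conclusion.** The point holds as an unsupported design assumption about a co-primary outcome. The article calls the sample sufficient for the 6MWT without stating a Lokomat-minus-PT difference, and relies on a figure that its own reasoning for the GMFM-66 shows to be the wrong kind.

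The size can be given only as a range. With 32 completers and 50 m (or 42.9 m) as the SD of the within-child difference, power for an assumed 15 m lies between 0.27 and 0.48; for 20 m at SD 50 m it is 0.47 or 0.59. Varying the correlation moves the two-sided figure for 15 m from 0.14 to 0.52. All of these are well below 0.80. A high correlation combined with a milder reduction could reach it (about 20 m at ρ = 0.75), so the claim is unsupported and not proven false.

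The plan for post hoc power is a distinct weakness. Power evaluated at the observed effect is a re-expression of the P value and cannot separate absence of effect from too small a trial. It applies to every outcome and does not depend on the 6MWT argument.

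**What to change.** Withdraw the sentence that calls the sample sufficient for the 6MWT. Alternatively, replace it with four stated items: the between-intervention 6MWT difference, the SD of the within-child difference (with its source or the assumed correlation), the sidedness of the 0.025 test, and the resulting power. For example: with 32 completers and an assumed within-child difference SD of 50 m, there is 80% power only for about 26 m (one-sided 0.025) or 28 m (two-sided 0.025). The sponsor must choose the sidedness and apply it to the GMFM-66 calculation as well, since two-sided 0.025 does not give 32.

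Separately, replace the post hoc power sentence in Analyses with a statement that non-significant results will be interpreted from the confidence interval of the between-intervention difference, against 3 points for the GMFM-66 and a prespecified reference difference for the 6MWT.

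The cost is two sentences and probably a less favourable stated property for the 6MWT. No more children need be enrolled.

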## Study aims and hypothesis

The primary aim of the study is to determine the impact on gait-related gross motor skills of a gait training program using a robotic-assisted gait trainer (the Lokomat^®^Pro) compared with a gait-related physiotherapy (PT) program for children in GMFCS Levels II and III. The primary hypothesis is that children receiving the Lokomat intervention will improve more on the GMFM-66 and 6-minute walk test (6MWT) than those in the gait-related PT program.

The secondary objective is to evaluate the comparative impact of Lokomat training and gait-related PT on: (a) individualized walking/gross motor based goals; (b) the amount/location of walking the child does each day (environmental context and season considered); (c) participation in activities and (d) health-related quality of life.

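### The 32-child requirement matches the stated alpha of 0.025 only as a one-sided z approximation; if the 0.025 threshold is two-sided, as an ANCOVA P value normally is, power at 32 is about 0.68, not 0.80

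*Protocol article*

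**What the plan says.** The Sample size section names a matched-pairs t test as the basis of the calculation. Its inputs are given as "With an alpha of 0.025, beta of 0.20, and a detectable change score difference between intervention of thre points on the GMFM-66", together with an SD of 6.0. The result is that "a sample of 32 children is required", raised to 40 for 20% drop-out or protocol deviation.

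The Analyses section plans that "a repeated measures ANCOVA will be performed on GMFM-66 and 6MWT change scores", with the relevant baseline score as covariate. On the significance level it says: "The P value will be adjusted to 0.025 to handle the expected high correlation between the GMFM-66 and timed walk". There are two co-primary outcomes, GMFM-66 and 6MWT.

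Neither section says whether 0.025 is one- or two-sided. The primary hypothesis, under Study aims and hypothesis, is worded in one direction: "children receiving the Lokomat intervention will improve more on the GMFM-66 and 6-minute walk test (6MWT) than those in the gait-related PT program".

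**The concern.** With two co-primary outcomes, a level of 0.025 looks like the conventional two-sided 0.05 split in half. An ANCOVA normally reports a non-directional P value, and the article mentions no one-sided test. A reader would therefore expect 32 to be the size for a two-sided 0.025 test. It is too small for that.

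Two things are at stake. One is the 80% power figure for the primary outcome. The Analyses section says that the power of analyses showing no difference will be determined post hoc, so power is meant to inform how a null result is read, and an overstated design figure invites over-reading it. The other is what 0.025 protects against, because that depends on sidedness.

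**Working it through.** **Inputs** (Sample size section unless noted)
- Difference 3 points, SD 6.0, so d = 3/6 = 0.5. The SD is taken here as that of the within-child difference between the two change scores.
- Alpha 0.025, sidedness not stated; the same 0.025 appears as the P-value threshold in Analyses.
- Beta 0.20, so z = 0.842.
- Matched-pairs t test; 32 evaluable, 40 enrolled.

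**Step 1: reproduce 32.** The z approximation is n = (z_alpha + z_beta)² / d².
- One-sided 0.025 (z = 1.960, the same as two-sided 0.05): (1.960 + 0.842)² / 0.25 = 31.4, so 32. This matches.
- Two-sided 0.025 (z = 2.241): (2.241 + 0.842)² / 0.25 = 38.02, so 39. No match.
- One-sided 0.05 (z = 1.645): (1.645 + 0.842)² / 0.25 = 24.7, so 25. No match.

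The drop-out step also reproduces: 32 / (1 − 0.20) = 40.

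**Step 2: use the test that the section names.** For a paired t test, power comes from the noncentral t distribution with n − 1 degrees of freedom and noncentrality d√n. At n = 32 the noncentrality is 0.5 × √32 = 2.83; at n = 40 it is 0.5 × √40 = 3.16.

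| Reading of 0.025 | n for 80% power, t (z) | Power at 32, t (z) | Power at 40, t (z) |
|---|---|---|---|
| One-sided | 34 (32) | 0.78 (0.81) | 0.87 (0.89) |
| Two-sided | 41 (39) | 0.68 (0.72) | 0.79 (0.82) |

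The z powers are Φ(d√n − z_alpha). For example, Φ(2.83 − 2.24) = Φ(0.59) = 0.72. Giving up one more degree of freedom for a period effect leaves the two-sided t figure at 32 at 0.68.

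**Step 3: the detectable difference.** With 32 children, two-sided 0.025 and 80% power, the paired t test detects 3.41 points, against the 3 points that the section treats as minimally important.

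**Step 4: the 6MWT.** The article quotes a mean gain of 25 m with SD 50 m. That is 25/50 = 0.5, the same standardised effect, so on those inputs the table applies to both co-primary outcomes.

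**Step 5: what 0.025 protects on each reading.**
- Two-sided 0.025 for each of two outcomes: 2 × 0.025 = 0.05, an overall two-sided 0.05.
- One-sided 0.025 for each: 2 × 0.025 = 0.05, an overall one-sided 0.05. Each test is then an ordinary two-sided 0.05 test read in one direction, so there is no allowance for two outcomes against an overall two-sided 0.05.

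**The case against.** The strongest objection is that the article never calls 0.025 two-sided and its hypothesis is directional. Read one-sided, the stated alpha, beta and sample size agree exactly by z and within two children by t. This stands to the extent that the power shortfall must be put conditionally. It does not make one-sided the natural reading. The planned test is an ANCOVA, no one-sided test is mentioned, two active treatments are compared, and the Background accepts that robotic training could turn out inferior if sessions are not interactive. A directional hypothesis states an expectation and does not specify a one-sided test.

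A second objection is that 0.68 is the low end of a range. Part of the gap is t against z (0.68 against 0.72). The drop-out allowance is described as generous, and some children who stop for study-related reasons stay in the primary analysis, so evaluable numbers may lie between 32 and 40. The baseline covariate may also help: a residual SD of about 5.3 instead of 6.0 (6.0 × 3/3.41), or about 23% less variance, would restore 80% at 32. All of this stands, although the article does not say how large a covariate gain to expect. For these reasons 0.68 should not be called the power that the planned ANCOVA will deliver.

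Two stronger readings are tempting and are not supported:
- **That the sizing has no allowance at all for two co-primary outcomes.** One-sided 0.025 per outcome is a valid Bonferroni split of one-sided 0.05. The allowance is absent only against an overall two-sided 0.05, and the article declares no overall level.
- **That the trial will run at a false-positive rate of 8 to 10%.** That follows from testing each outcome at two-sided 0.05 (with independent outcomes, 1 − 0.95² = 0.0975). The article sets the threshold at 0.025, so this describes a plan that it does not contain.

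**Conclusion.** The point holds in conditional form. The figure of 32 comes only from a z approximation at one-sided 0.025, and the paired t test named as its basis does not give 32 on either reading. One-sided, the gap is minor: 34 needed and power 0.78 at 32. On the natural two-sided reading it is material: nine more evaluable children (41 − 32), or about 12 points of power (0.80 − 0.68).

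The two-sided figures assume d = 0.5 with SD 6.0 correct for the within-child difference, a paired t test, 32 evaluable children and no gain from covariate adjustment. If SD 6.0 is instead the SD of change under each treatment, the SD of the difference is 6√(2(1 − rho)), where rho is the within-child correlation between the two change scores; it equals 6 only at rho = 0.5. Power at 32 would then run from 0.37 (rho = 0) to 0.94 (rho = 0.75). That is a separate question and does not alter the mismatch shown here.

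The documents do not settle which sidedness was meant, so the Sample size and Analyses sections need to be reconciled before a null result is interpreted.

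**What to change.** State in both the Sample size and Analyses sections that each co-primary test is two-sided at 0.025. Replace the 80% claim with power of about 0.68 at 32 evaluable children and 0.79 if all 40 are evaluable, before any gain from covariate adjustment. Alternatively, restate the difference detectable with 80% power at 32 as about 3.4 points.

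If a one-sided test is truly intended, say so in both sections, declare the overall one-sided 0.05 level, and give power at 32 as about 0.78.

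Either route is a change of wording with no change in enrolment. The cost is a less favourable stated power.

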Due to the lack of expectation of return to baseline in the break period, a second analytic approach will be taken as well using a generalized estimating equation (GEE) adjustment for repeated measures within subjects analysis (Baker et al. 2007). In this approach treatment effects are evaluated via regression analysis and the GEE method will allow the fit of two models. The first is for treatment effect, treatment-period effect, and differential carryover effect adjusting for the baseline scores, and the second is treatment effect and treatment-period effect with exclusion of any differential carryover effect. Factors hypothesized a priori to be associated with GMFM-66 change score magnitude will be entered within this model using a forward stepwise regression procedure, e.g., age, GMFCS Level, motivation (DMQ) score, ASK baseline score.

Finally, a third approach will be taken if there is significant evidence of a carryover effect and significant interaction effects. This will be to focus on the data from the first arm of the study, i.e., an ANCOVA adjusted for baseline GMFM-66 change scores of just the first intervention period (randomisation to either Lokomat or PT with 20 children per group). This comparison in itself would have a power of about 0.60 for the GMFM-66 (with alpha = 0.025 and a medium effect size of 0.50).

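### The requirement of 32 children reproduces only if the unstated sidedness of the 0.025 level is one-sided; on the more natural two-sided reading, power is about 0.68 to 0.79

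*Protocol article*

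**What the plan says.** The Sample size section takes the paired t test as its basis ("sample size calculations that link with a matched pairs *t* test calculation are appropriate"). The target is to "detect a difference between the two interventions of three points (SD = 6: small effect size) on the GMFM-66". The error rates are given as "With an alpha of 0.025, beta of 0.20", and the result is "with an estimated SD of change of 6.0 points), a sample of 32 children is required". The allowance for losses follows: "We increased the sample requirement to 40 to account for a potential drop out/protocol deviation rate of 20" per cent.

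The Analyses section plans a repeated measures ANCOVA of the change scores, with the relevant baseline as covariate, for each of the two co-primary outcomes. It sets the level this way: "The P value will be adjusted to 0.025 to handle the expected high correlation between the GMFM-66 and timed walk". For the fallback analysis of the first period alone, with 20 children per group, it says that the comparison "would have a power of about 0.60 for the GMFM-66 (with alpha = 0.025 and a medium effect size of 0.50").

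No section says whether 0.025 is one- or two-sided. The primary hypothesis in Study aims and hypothesis is directional: more improvement with the Lokomat than with PT.

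**The concern.** The Sample size and Analyses sections use the same number, 0.025, but 32 does not fit the most natural meaning of that number in the Analyses section. A threshold adjusted to 0.025 because there are two outcomes looks like the usual two-sided 0.05 divided by two. A sample of 32 is what one gets with no such division, at two-sided 0.05.

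Three points on the GMFM-66 is presented as the minimally important difference that the trial is powered to detect, and the Analyses section plans to comment on power when no difference is found. If the design power is nearer 0.7 than 0.8, a null result would be given more weight than it deserves.

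Two related statements add to the uncertainty. The 6.0 is called an SD of change, but a paired calculation needs the SD of the within-child difference between two changes. And high correlation between two outcomes is not a reason to lower the threshold: testing two outcomes is the reason, and correlation only makes a fixed halving more conservative.

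**Working it through.** **Inputs (Sample size section).** Difference δ = 3 points; SD = 6.0, used as the SD of the paired difference, so d = 3/6 = 0.50; power 0.80; alpha 0.025, sidedness not given; losses 20%.

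**Reproducing the plan's figure.** Normal approximation: n = ((z_alpha + z_power) × SD/δ)², with z_power = 0.842 and SD/δ = 2.

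- One-sided 0.025 (same critical value as two-sided 0.05): z_alpha = 1.960; n = (2.802 × 2)² = 31.4, so 32. This matches.
- Two-sided 0.025: z_alpha = 2.241; n = (3.083 × 2)² = 38.0, so 39. This does not match.
- One-sided 0.05: n = 24.7, so 25. This does not match.

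The inflation reproduces: 32/(1 − 0.20) = 40.

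**Exact paired t test.** Noncentral t with n − 1 degrees of freedom and noncentrality 0.50 × √n.

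| Level | n for 80% power | Power, n = 32 | Power, n = 40 |
|---|---|---|---|
| One-sided 0.025, or two-sided 0.05 | 34 | 0.78 | 0.87 |
| Two-sided 0.025 | 41 | 0.68 | 0.79 |

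At two-sided 0.025 with 32 children, the difference detectable with 80% power is 3.4 points. By the normal approximation, power at 32 is 0.72 instead of 0.68. Enrolling enough to keep 41 evaluable after 20% loss would take 41/0.80 = 51.25, so 52.

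**What if 6.0 is the SD of one change score?** Then the SD of the within-child difference is 6 × √(2(1 − ρ)), where ρ is the correlation between a child's two change scores. The protocol gives no ρ, so the values below are assumptions.

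| Assumed ρ | SD of difference | Power, n = 32, two-sided 0.025 | Power, n = 32, one-sided 0.025 |
|---|---|---|---|
| 0 | 8.49 | 0.37 | 0.49 |
| 0.25 | 7.35 | 0.49 | 0.61 |
| 0.5 | 6.00 | 0.68 | 0.78 |
| 0.75 | 4.24 | 0.94 | 0.97 |

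The plan's use of 6.0 in a paired calculation agrees with this reading only at ρ = 0.5.

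**Can the first-period statement settle which SD is meant?** An unadjusted two-sample t test with 20 per group and effect size 0.50 has power 0.24 at two-sided 0.025 and 0.34 at one-sided 0.025. Neither is near the stated value of about 0.60, so that statement cannot settle it.

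**Holm against a fixed 0.025 for each outcome.** Holm compares the smaller P with 0.025 and, if that is significant, the other with 0.05. Whatever the fixed split rejects, Holm also rejects, so power cannot fall. For illustration, assume 32 children, d = 0.50 on both outcomes, two-sided tests, and a correlation of 0.6 between the outcomes. By simulation, power for the GMFM-66 rises from 0.68 to 0.74, and power for both outcomes from 0.55 to 0.66. Neither the correlation nor the 6MWT effect size comes from the protocol, which gives only a single-group 6MWT gain.

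**The case against.** The strongest reply is that nothing in the protocol says two-sided. The hypothesis is directional, and at one-sided 0.025 the plan's own inputs give exactly 32 by a standard approximation. A reader might infer that the sample size is simply wrong and that the true power is 0.68 instead of 0.80. The documents do not support that, because it turns a reading of the level into a stated fact. This part of the reply stands, and the finding is conditional for that reason.

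It does not make the text adequate. A directional hypothesis is not a specification of a one-sided test, and none is announced. The usual ANCOVA F test is non-directional. One-sided 0.025 also equals two-sided 0.05 for each outcome, so the sample size would then carry no multiplicity allowance relative to the conventional two-sided 0.05, although the Analyses section says that an adjustment is made.

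It is also fair to say that 0.68 is the low end. It needs the full 20% loss, which the plan calls generous, and the primary analysis keeps children who stop for study-related reasons. Baseline adjustment may add precision. The range 0.68 to 0.79, before any such gain, is therefore the right statement.

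A reader might further infer that 6.0 has been used in two incompatible ways, since 3/6 equals the 0.50 in the first-period statement. That is only suggestive. The Analyses section never derives 0.50 from 3/6; it calls 0.50 medium where the Sample size section calls 3 with SD 6 small; and its power figure does not reproduce from an unadjusted 0.50. What remains is a need to define the SD.

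Finally, a fixed 0.025 for each outcome controls the familywise error at 0.05 whatever the correlation, so the stated rationale is a flaw of wording and not an error in the test. Holm is an improvement, not a repair of validity, and simple simultaneous confidence intervals would no longer match the tests exactly.

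**Conclusion.** The concern holds in conditional form. With a difference of 3 and an SD of 6.0, 32 is the answer only for one-sided 0.025 (equivalently two-sided 0.05), and only by normal approximation. If 0.025 is two-sided, which is the better reading of the Analyses section, the design falls short of its stated 80% power for 3 points by about 12 percentage points at 32 evaluable children and by about 1 at 40.

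This rests on 6.0 being the SD of the within-child difference and on the paired t test as the planning model, with no credit for baseline adjustment. If 6.0 is the SD of one change score, power depends strongly on an unstated correlation under either sidedness. The matter should be fixed. It is not critical, because type I error, enrolment and the analysis itself do not depend on it.

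**What to change.** 1. State whether 0.025 is one- or two-sided, the same way in the Sample size and Analyses sections.
2. If two-sided, restate the power for 3 points as 0.68 to 0.79 for 32 to 40 evaluable children, with 80% power for about 3.4 points at 32. If one-sided, say so and give 0.78 at 32.
3. State that 6.0 is the SD of the within-child difference between the two change scores. If it is the SD of one change score, give the short table of power over assumed between-period correlations instead.
4. Replace the correlation rationale with multiplicity control for two co-primary outcomes, and test them by Holm: the smaller P against 0.025, then the other against 0.05. The familywise error stays at 0.05.

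The cost is a few sentences, a less favourable stated power if the test is two-sided, and slightly less convenient confidence intervals under Holm. No children are added.
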